# Laser hair depilation for the prevention of disease recurrence in adolescents and young adults with pilonidal disease: study protocol for a randomized controlled trial

**DOI:** 10.1186/s13063-018-2987-7

**Published:** 2018-11-01

**Keywords:** Pilonidal disease, Laser hair depilation, Recurrence, Randomized controlled trial

## Abstract

**Background:**

Laser hair depilation is a promising therapy in the management of pilonidal disease. However, the large controlled trials needed to demonstrate the effectiveness of this practice have not been performed.

**Methods:**

We designed a single-center randomized controlled trial that will enroll 272 patients with pilonidal disease. Patients will be randomized to receive laser hair depilation of the sacrococcygeal region or the best recommended standard of care. The primary outcome is the rate of recurrent pilonidal disease at 1 year, defined as development of a new pilonidal abscess, folliculitis, or draining sinus after treatment, which would require antibiotic treatment, additional surgical incision and drainage, or excision within 1 year of enrollment. Secondary outcomes include each of the following at 1 year: disability days of the patient, disability days of the caregiver, health-related quality of life, healthcare satisfaction, disease-related attitudes and perceived stigma, pilonidal disease-related complications, pilonidal disease-related procedures, surgical excision, postoperative complications, and compliance with recommended treatment.

**Discussion:**

This study will determine the effectiveness of laser hair depilation to reduce pilonidal disease recurrence in adolescents and young adults as compared to the best recommended standard of care.

**Trial registration:**

ClinicalTrials.gov, NCT03276065. Registered on 8 September 2017.

**Electronic supplementary material:**

The online version of this article (10.1186/s13063-018-2987-7) contains supplementary material, which is available to authorized users.

## Background

Pilonidal disease is a common infectious condition in the adolescent and young adult population, affecting approximately 1% of individuals aged 15–30 years [1–3]. The disease is believed to be caused by the insertion of loose hairs into the natal cleft, resulting in a chronic foreign body reaction and the formation of epithelialized tracts and midline pits [4]. Guidelines for the medical management of pilonidal disease support meticulous hygiene to the sacrococcygeal area and routine hair removal by mechanical or chemical depilation [5]. However, compliance with these recommendations is low, and patients frequently suffer considerable morbidity related to disease recurrence [6].

Laser hair depilation has been studied as a strategy to decrease pilonidal disease recurrence rates. Several studies have demonstrated the efficacy of laser hair depilation to reduce pilonidal disease recurrence compared to standard of care in both adults and children [7–18]. These studies conclude that laser hair depilation is a useful adjunct in preventing recurrence; however, most of these studies were small, retrospective, or not sufficiently controlled, and many of the authors have called for additional well-controlled prospective randomized controlled trials (RCTs) in a broader population [11, 15, 19, 20].

We therefore designed a prospective, RCT to determine the effectiveness of laser depilation in reducing pilonidal disease recurrence compared to the best recommended standard of care. In addition to recurrent disease, this trial will evaluate other outcomes important to patients, including disease-related disability, the need for procedures such as surgical excisions or drainage procedures, health-related quality of life (HRQOL), healthcare satisfaction, and disease-related attitudes and perceived stigma.

## Methods

### Study design

This is a prospective RCT comparing two currently available treatment options for patients with pilonidal disease. The control group receives the best recommended standard of care. The intervention group receives laser therapy in addition to the best recommended standard of care. The control group treatment regimen is based on recommendations from published studies and guidelines [3, 5, 15, 21, 22]. The intervention group treatment regimen was designed based on the interventions described in previously published studies and a pilot study we previously performed at Nationwide Children’s Hospital (NCH) [7–17, 23].

### Stakeholder team

As this study was designed to assess outcomes related to pilonidal disease that are important to patients and their families, we designed this trial with significant input from a multi-disciplinary stakeholder group that includes patients, caregivers, community-based pediatricians, emergency medicine physicians, adult and pediatric surgeons, and nurses. We engage our stakeholder partners through in-person individual interviews and stakeholder group meetings to discuss planning and conducting the study and disseminating results. In-person stakeholder meetings are held semiannually to provide insight into issues related to study design, recruitment, retention, study progress, and developing plans for dissemination of the results.

### Study population

Inclusion and exclusion criteria for the trial are listed in Table 1. Patients aged 12–21 years with a diagnosis of pilonidal disease are eligible for participation. The inclusion criteria were chosen to capture patients with the highest incidence of pilonidal disease and who have the highest likelihood of tolerating the laser treatment. In addition, all patients with pilonidal disease are included without regard for the number of previous episodes of disease or surgical history. Patients with a history of photosensitivity are ineligible for the study, and those with an acutely inflamed pilonidal sinus, cyst, or abscess are invited to participate upon resolution of their acute episode of disease. After determining that all eligibility criteria are met, a trained member of the research team invites the patient and legal guardian to enroll.

**Table 1 Tab1:** Eligibility criteria

Inclusion criteria	
• Age 12–20 years	
• Diagnosis of pilonidal disease	
Exclusion criteria	
• History of photosensitivity	
• Actively inflamed pilonidal sinus (these patients will be informed of the trial and invited to contact the study team upon resolution of their inflamed sinus if they are interested in being in the trial at that time)	

### Study setting

This trial is underway at our institution. Adolescents and young adults with pilonidal disease in the Columbus, Ohio metropolitan area are recruited from the clinics, emergency departments, and inpatient units at NCH and the Ohio State University (OSU) Wexner Medical Center, and from the clinics of community pediatric practices.

### Randomization methods

Our randomization sequence was created using a randomized block scheme, with blocks of size four or six selected randomly with equal probability. The sequence was built using the plan procedure in SAS 9.4 (SAS Institute Inc., Cary, NC, USA). It was generated and is maintained by the project statistician and is unavailable to other research study members. After study staff verify patient eligibility (further described below) and obtain informed consent, patients wishing to enroll in the trial are randomized within the web-based Research Electronic Data Capture (REDCap) system using the earlier generated randomization list [24].

### Baseline assessment

After verification of eligibility by initial phone interview and again at the first clinic visit prior to randomization and treatment, both the patient and legal guardian are asked to provide demographic and socioeconomic information including age, race, ethnicity, gender, annual household income range, patient occupation (from those engaged in paid employment), guardian occupations, and specific insurance coverage. We also collect a complete medical history of pilonidal disease, family history of pilonidal disease, current pilonidal disease symptoms, current hygiene regime, and history of physician office visits, emergency department/urgent care visits, and inpatient hospitalizations for pilonidal disease. A sample list of the collected data points is provided in Table 2. At the initial clinic visit, a physician member of the research team (1) reviews the study protocol and procedures, (2) explains the risks and benefits of each treatment, (3) answers questions, and (4) obtains written informed consent and assent (for patients < 18 years of age). The child and legal guardian are asked to complete the age-appropriate Pediatric Quality of Life Inventory (PedsQL™) and questions about healthcare-associated disability, pain, and pilonidal disease management. The patient also completes the Child Attitude Toward Illness Scale (CATIS), and the parent and child complete the disease-related stigma scales. Patients are then randomized and informed of their treatment arm.

**Table 2 Tab2:** Sample of data to be collected

• Demographics (including age, gender, body mass index, race, ethnicity, caregiver education level, employment status, income, marital status, number of household residents)	
• Fitzpatrick skin type	
• Vital signs	
• Laboratory testing	
• Episodes of pilonidal disease	
• Surgical procedures performed for pilonidal disease	
• Symptoms	
• Medications	
• Complications (if any)	
• Readmissions	
• Recurrence	
• Days missed from work or school	
• Days missed from normal activities	
• Office visits referable to pilonidal disease	
• Emergency department visits for pilonidal disease	
• Treatment-related pain	

### Treatment arms

#### Control group

Subjects randomized to the control group receive standardized education and training about hair removal, reflective of the best recommended standard of care. Patients and families in the control group are taught hair removal techniques, and the technique of mechanical depilation is demonstrated for the patient and caregiver with the nurse or physician shaving the gluteal cleft of the patient during this visit. It is recommended that they perform either chemical or mechanical depilation as needed to keep the area hair-free. They are given supplies in clinic to be able to perform hair removal for the next 6 months. Furthermore, the patient and family are given the option to schedule additional in-person visits for further education and training on hair removal as desired.

#### Intervention group

Similar to the control group, the patients and families in the intervention group are taught hair removal techniques at the initial visit and asked to perform either chemical or mechanical depilation as needed to keep the area hair-free between clinic treatments. Fitzpatrick skin type classification is assessed at the first treatment visit and used to select the best laser to perform hair removal for each patient [7–17, 23]. A 7% lidocaine/7% tetracaine cream is applied 45 min prior to treatment to minimize any discomfort associated with the heat of the laser treatments. Patients receive either an 810 nm (for Fitzpatrick skin types I–IV) or Nd:YAG (for Fitzpatrick skin types V–VI) 28 joule application at auto pulse duration for 400 ms. Subjects randomized to the laser depilation arm visit the surgery clinic for one treatment every 4–6 weeks to receive a total of five treatments. The energy settings of the laser are sequentially increased at each visit in order to maximize the depilation effect.

### Outcomes

The primary outcome is pilonidal disease recurrence at 1 year, defined as development of a new pilonidal abscess, folliculitis, or draining sinus after treatment, which would require antibiotic treatment, additional surgical incision and drainage, or excision. Secondary outcomes include each of the following at 1 year: disability days of the patient, disability days of the caregiver, HRQOL, healthcare satisfaction, disease-related attitudes and perceived stigma, pilonidal disease-related complications, pilonidal disease-related procedures, surgical excision, postoperative complications, and compliance with recommended treatment.

### Assessments and follow-ups

Figure 1 shows a schematic overview of the study. The Standard Protocol Items: Recommendations for Interventional Trials (SPIRIT) checklist is provided in Additional file 1. Each patient is involved in the study for 1 year. All patients visit the surgery clinic for an initial visit. Subsequently, patients randomized to the laser group are seen for additional visits for laser treatments every 4–6 weeks until they receive a total of five treatments. Patients in the control group have monthly follow-up at 1, 2, 3, and 4 months by phone or email with the option to schedule additional in-person visits as desired. We continue to follow up with all participants at 6, 9, and 12 months from the initial treatment. Study staff conduct data collection at each follow-up time point. Figure 2 details the schedule of enrollment, interventions, and outcomes assessed at each time point.

**Fig. 1 Fig1:**
[figure not shown]
Study overview

**Fig. 2 Fig2:**
[figure not shown]
Schedule of enrollment, interventions, and assessments over the study period (SPIRIT statement). *At the discretion of the patient or caregiver

#### Post laser treatment follow-up

Immediately following each laser treatment and 24 h after, the patient is asked to rate their pain from 1 to 10 utilizing the numeric rating scale (NRS). The immediate postprocedure pain score is obtained in person at the conclusion of the laser procedure, while the 24 h pain score is communicated to the study team by text message, email, or phone call the following day.

#### Follow-up at 1, 2, 3, and 4 months

The patient and legal guardian complete surveys assessing healthcare-associated disability, pain, pilonidal disease management, and emergency department/urgent care/physician office/hospital visits that occurred between follow-up assessments. In addition, the CATIS is completed at the 2 months follow-up, the parent and child disease-related stigma scales are completed at the 3 months follow-up, and the ageappropriate Child and Parent PedsQL™ is administered at the 4 months follow-up. The healthcare satisfaction questionnaire is administered at the 1 and 4 months follow-ups. These surveys and questionnaires are completed at the in-person visits for patients in the laser group and by either phone or email/web-based survey for patients in the control group (unless they scheduled an in-person visit for any of these follow-ups, in which case they are completed at the in-person visit).

#### Follow-up at 6, 9, and 12 months

Each participant receives an email or telephone call at 6, 9, and 12 months after their initial visit. Follow-up is conducted by email/web-based survey or by phone with a member of the research team from NCH. The patient and legal guardian complete surveys assessing disability days, pain, pilonidal disease management, and emergency department/urgent care/physician office/hospital visits that occurred between follow-up assessments. At 6 and 12 months, the age-appropriate Child and Parent PedsQL™ and the CATIS are administered. At 9 months, healthcare satisfaction and disease-related stigma scales are administered.

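### Healthcare satisfaction and perceived stigma are set as 1-year secondary outcomes, but the text schedule last measures both at 9 months

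*Protocol article*

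**What the plan says.** The Outcomes section opens its list with "Secondary outcomes include each of the following at 1 year". Among the items that follow are "healthcare satisfaction, disease-related attitudes and perceived stigma, pilonidal disease-related complications". The abstract gives the same list and the same time point, including "health-related quality of life, healthcare satisfaction, disease-related attitudes and perceived stigma".

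The schedule is spread over three sections:

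- Baseline assessment: "the parent and child complete the disease-related stigma scales". Satisfaction is not named there.
- Follow-up at 1, 2, 3, and 4 months: "The healthcare satisfaction questionnaire is administered at the 1 and 4 months follow-ups", and "the parent and child disease-related stigma scales are completed at the 3 months follow-up".
- Follow-up at 6, 9, and 12 months: "At 9 months, healthcare satisfaction and disease-related stigma scales are administered". The same section assigns the PedsQL and the CATIS to months 6 and 12. The general surveys at all three contacts cover disability days, pain, management of the disease and healthcare visits.

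The Analytic plan compares continuous secondary outcomes between arms by Mann-Whitney U tests. It expects the laser arm to do better on satisfaction and on attitudes and stigma. Mixed models of the full trajectory of these scales are planned as exploratory.

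**The concern.** Satisfaction and stigma are scores taken at a moment, so an outcome at 1 year needs a measurement at or near 1 year. The text plans none. A Mann-Whitney comparison uses one value per patient, and the Analytic plan names no other month for these scales. Whoever runs the analysis would have to report a 9-month score as a 1-year result, redefine the outcome, or leave it out.

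The Background names both among the outcomes that matter to patients, and the Analytic plan gives them a direction in advance. Patients are told their arm at the first visit, and an interim analysis is planned once 34 patients per group have completed their year. A change of time point is easier to defend if made and recorded before arms are compared. A 12-month score that was not collected cannot be recovered afterwards.

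**Working it through.** No power, sample size or alpha figure enters this point. The check sets the months at which each scale is given against the month at which its outcome is defined. All months come from the Baseline assessment section and the two follow-up sections.

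| Scale | Outcome it serves | Months given | Last month | Defined at | Gap |
|---|---|---|---|---|---|
| PedsQL | Quality of life | 0, 4, 6, 12 | 12 | 12 | 12 − 12 = 0 |
| CATIS | Attitudes to illness | 0, 2, 6, 12 | 12 | 12 | 12 − 12 = 0 |
| Stigma scales | Perceived stigma | 0, 3, 9 | 9 | 12 | 12 − 9 = 3 months |
| Satisfaction questionnaire | Healthcare satisfaction | 1, 4, 9 | 9 | 12 | 12 − 9 = 3 months |

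The pairing of the CATIS with the attitudes outcome is read from the name of the scale.

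Could another planned source supply a 12-month value?

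1. The general survey at month 12 names no satisfaction or stigma items.
2. The Medical record review at 1 year gathers clinical data and episodes of care. It cannot yield a patient-reported score.
3. The exploratory mixed models would have no observation of either scale after month 9, so a 12-month estimate from them would be extrapolation.

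How much of the outcome list is affected? The Outcomes section lists ten items: patient disability days, caregiver disability days, quality of life, satisfaction, attitudes and stigma (one joint item), complications, procedures, excision, postoperative complications, and compliance. Satisfaction is affected in full. The joint item is affected in its stigma part only. That is one item and part of a second, out of ten.

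How many patients could still be covered? Trial status reports enrolment from September 2017 and more than 50 of 272 enrolled by 25 October 2018. The number still to enrol at that date was therefore below 272 − 50 = 222; the exact number is not given. Only patients enrolled by about 25 October 2017, in roughly the first two months of recruitment, could already have reached month 12.

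**The case against.** The strongest reply is that this is a labelling mismatch on supporting outcomes. Both scales are collected at month 9, in both arms, by the same remote route, so the schedule treats the arms alike and a 9-month comparison is feasible. One of the two remedies is simply to write 9 months in the outcome list. This stands, and it limits the weight of the point.

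A second reply is that the 1-year label is loose. It also covers cumulative items such as disability days and procedures, where it can only mean over the year of follow-up. On that reading the last scheduled score would serve. This is plausible as an intention, but the article does not say so. With three satisfaction assessments and two stigma assessments after baseline, a score somewhere within the year does not identify which one is compared.

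A third reply is that Fig. 2, which sets out the schedule, is not visible in the copy reviewed. A reader might infer from the text that no 12-month value will exist for anyone. That goes too far, because the figure might show a 12-month administration. If it does, it conflicts with the follow-up section and the two must be reconciled. If it does not, the outcome list and the schedule conflict.

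A fourth reply is that the analysis plan may name the analysed visit. It may, but it cannot supply scores that were not collected. The conflict lies between two statements that the article itself makes.

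**Conclusion.** The article is wrong as written, with moderate severity. On the text schedule, healthcare satisfaction and the stigma part of the joint attitudes and stigma item cannot be compared at 1 year, because their last measurement is 3 months earlier. The primary outcome and the sample size do not depend on this.

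Three stronger readings are not supported:

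- That two whole secondary outcomes are lost. Stigma is half of a joint item, and the other half has a 12-month measurement.
- That the outcomes cannot be analysed at all. They can be compared at 9 months, though not as the outcome defined.
- That the team will pick a time point after seeing results. Nothing in the article suggests it, and each scale has only one assessment after month 4, which leaves little room for selection.

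The conclusion rests on the follow-up sections being the operative schedule and on the 1-year label meaning month 12 for scores taken at one moment. What the trial registration says about these time points is not known here.

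**What to change.** Choose one of two changes.

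- Add the satisfaction questionnaire and the parent and child stigma scales to the 12-month email or telephone survey, and amend the section on follow-up at 6, 9, and 12 months. The contact already takes place, so the cost is an amendment and some added burden for respondents at a contact that already carries the PedsQL and the CATIS. Patients already past month 12 will have only a 9-month value, and the analysis should say how they are handled.
- If the spacing of questionnaires is deliberate and the burden is not acceptable, restate satisfaction and perceived stigma as 9-month outcomes in the abstract and the Outcomes section, keeping attitudes (CATIS) at 12 months. This needs no new data, but gives up the 1-year result for these two measures.

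Either change should be made and dated before any comparative look at the data. Fig. 2 should be checked at the same time so that the figure, the outcome list and the schedule agree. If other records of the trial carry the same 1-year label for these measures, they should be aligned too.

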#### Medical record review

A medical record review is performed for each patient by a trained member of the research team at the 1 year follow-up, to collect the data detailed in Tables 1 and 2. We record all episodes of care related to pilonidal disease including inpatient and outpatient encounters. If the medical record and patent/caregiver report are discordant, we will ask the patient/caregiver about any discordant episode. If the reports remain discordant, the medical record documentation of medical endpoints (e.g., disease recurrence, wound breakdown) is used in the data analyses.

